### Outcome measures

The primary outcome and its definition are described in detail below. Pre-specified secondary outcomes are presented in Table 2 below, each with its definition, instrument or data source, timing of ascertainment, and analytic role.

**Table 2 pone.0356813.t002:** Pre-specified primary and secondary outcomes.

Outcome	Definition	Instrument / Data Source	Timing of Ascertainment	Priority	Analytic Role
**Time to fecal continence**	First clinic visit (confirmed at subsequent visit) at which the participant meets social continence threshold: BCS criteria (ARM) or BFS ≥ 17 (HD), from date of definitive repair	BCS (ARM) [16] or BFS (HD) [17], parent/caregiver proxy to age 11; self-report from age 12	Annual visits from age 3	**PRIMARY**	Kaplan–Meier estimation; Cox proportional hazards regression; Fine-Gray model for competing risks; landmark analyses at ages 5 and 10
HD-associated enterocolitis (HAEC)	≥1 physician-confirmed episode meeting Ruttenstock criteria requiring medical treatment	Clinical record review; REDCap adverse event log	Each annual visit; first episode date recorded	Secondary 1	Cox regression / Fine-Gray competing risks; descriptive incidence rate
Reoperation rate	Any unplanned surgical return to the operating room following index repair	Operative report review; REDCap surgical procedure log	Cumulative from index repair; each annual visit	Secondary 2	Cox regression / Fine-Gray competing risks; cumulative incidence curve
Disease-specific quality of life	HAQL total score and subscale scores (age-appropriate version)	HAQL questionnaire, self- or proxy-report [18]	Ages 6, 10, and 14 years	Secondary 3	Linear mixed-effects model (repeated measures); descriptive means by group
Transition readiness	Transition Readiness Assessment Questionnaire	TRAQ [19], self-report	Ages 14 and 17 years	Secondary 4	Linear mixed-effects model; descriptive score trajectory
Loss to follow-up (LTFU)	No clinic encounter, survey, or successful contact for ≥18 months while under age 18 and not yet transitioned	REDCap contact log; clinic attendance record	Flagged at 18-month mark; reviewed at each annual analysis	Secondary 5	Logistic regression (ever-lost vs retained); descriptive LTFU rate

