The primary outcome is time to achievement of fecal continence from the date of definitive surgical repair, analysed as a time-to-event outcome. For participants with ARM, continence is assessed using the Baylor Continence Scale (BCS) [16], with social continence defined as no soiling episodes in the preceding 4 weeks per published BCS criteria, completed by the parent or caregiver proxy up to age 11 and by self-report from age 12. For participants with HD, continence is assessed using the Bowel Function Score (BFS) [17], with social continence defined as a BFS score ≥ 17, administered to the parent or caregiver proxy up to age 11 and by self-report from age 12. Both instruments are administered at every annual clinic visit beginning at age 3 years. The earliest clinically meaningful assessment for continence is age 3, consistent with normal developmental milestones for voluntary bowel control. Participants will be censored at age 18, death, transition to adult care, or loss to follow-up, whichever occurs first.

Pre-specified secondary outcomes, listed in priority order, are: (1) Hirschsprung-associated enterocolitis (HAEC), defined as at least one physician-confirmed episode meeting the Ruttenstock diagnostic criteria and requiring medical treatment, assessed at each annual visit [20]; (2) reoperation rate, defined as any unplanned surgical return to the operating room following index repair, assessed cumulatively; (3) disease-specific quality of life, measured using the HAQL [18] at ages 6, 10, and 14 years using age-appropriate versions; (4) transition readiness, assessed at ages 14 and 17 years using the validated Transition Readiness Assessment Questionnaire (TRAQ) [19], and (5) loss to follow-up rate, defined operationally in the Loss to Follow-Up section. Each secondary outcome will be reported descriptively and, where the events-per-variable threshold is met (see Sample Size section), included as an endpoint in pre-specified multivariable analyses with the analytic role specified in the Statistical Analysis section.

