### Loss to Follow-Up

A participant will be considered lost to follow-up if there has been no clinic encounter, completed survey, or successful contact (by telephone, email, or mail) for 18 or more consecutive months in a participant aged under 18 years who has not yet transitioned to adult care or withdrawn from the registry.

When a participant misses a scheduled visit without prior notification, the research assistant will initiate a standardised re-contact sequence: (1) two phone call attempts within 2 weeks; (2) email or written letter within 4 weeks, if contact information is on file; and (3) two further phone call attempts at 3 months. If no successful contact is made after this full sequence, the participant will be flagged as lost to follow-up in REDCap with the date of last confirmed contact recorded. All contact attempts and outcomes will be logged prospectively.

Rates and timing will be reported descriptively at each annual analysis. In survival and longitudinal analyses, the loss will be treated as censoring at the date of last confirmed contact. The potential impact of informative (non-random) censoring will be examined using inverse probability weighting (IPW) as a sensitivity analysis [26,27]. Factors independently associated with the loss will be examined using logistic regression (ever-lost vs retained) as a secondary analysis, with candidate predictors pre-specified to include: diagnosis type, age at enrollment, sex, aganglionosis length or ARM Krickenbeck category, area-level deprivation quintile, and distance from COCOE.

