### Survey administration and burden mitigation

The six instruments have a combined estimated completion time of 54–95 minutes depending on age and programme status. To reduce burden, instruments are administered in a staggered fashion across visits: the HAQL, BCS and BFS are prioritised at each visit; the PedsQL modules and PECI are administered at alternating annual visits; and the PREOM-BMP is administered only to eligible families. Where possible, surveys are distributed electronically via REDCap prior to the clinic visit to allow completion at home, reducing in-clinic time. Paper versions are available for families without internet access, and a trained research assistant is available to assist with completion where literacy or language is a barrier. Surveys are available in English and French. In the event of partial completion, available items will be scored according to the instrument's published scoring guidelines; instruments with fewer than the minimum required items completed will be recorded as missing and addressed per the missing data plan in the Statistical Analysis section. Based on experience from comparable paediatric surgical registries, we anticipate an instrument completion rate of approximately 70–80% per visit; completion rates will be reported at each annual analysis.

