**Objective 3:** Factors associated with key outcomes. Time to achievement of fecal continence will be estimated using the Kaplan–Meier method, with curves reported separately for ARM and HD given the use of disease-specific instruments. Given the embryological, surgical, and prognostic distinctions between the two conditions, and the use of disease-specific continence instruments, multivariable analyses will be conducted separately for ARM and HD rather than as a single combined model. For each disease cohort, a Cox proportional hazards model will be fitted with disease-appropriate pre-specified candidate predictors: for ARM, Krickenbeck category, age at index repair, sex, syndromic status, and area-level deprivation quintile; for HD, length of aganglionosis, age at index repair, sex, syndromic status, and area-level deprivation quintile. The proportional hazards assumption will be tested for each model using Schoenfeld residuals. Where competing risks are present (death or transition prior to the continence event), the Fine-Gray subdistribution hazard model will be applied within each cohort. Pre-specified landmark analyses will report the proportions achieving continence by age 5 and age 10 for each disease, to allow benchmarking against published ARM and HD cohort data. For each disease-specific model, multivariable Cox regression will be triggered only once the events-per-variable (EPV) threshold of 10 is met within that cohort at interim review; otherwise analyses for that cohort will be limited to descriptive and unadjusted comparisons.

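### Continence is found only at annual visits but analysed as if its onset date were known, so the proportion continent by age 5 is biased downward or at best unbiased, by an amount the protocol does not let one fix

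*Protocol article*

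**What the plan says.** All references are to the protocol article.

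- **Event date.** Table 2 (Outcome measures) defines the primary event as "First clinic visit (confirmed at subsequent visit) at which the participant meets social continence threshold". The later visit confirms the event; nothing says that it moves the date.
- **Assessment schedule.** Outcome measures: "Both instruments are administered at every annual clinic visit beginning at age 3 years". For ARM the criterion looks back only a month: "social continence defined as no soiling episodes in the preceding 4 weeks per published BCS criteria". It cannot place onset within a gap of a year.
- **Completion.** Survey administration and burden mitigation: "we anticipate an instrument completion rate of approximately 70–80% per visit".
- **Estimator.** Statistical analysis, Objective 3: "Time to achievement of fecal continence will be estimated using the Kaplan–Meier method", with Cox models for each disease and Fine-Gray where there are competing risks.
- **Landmarks.** The same section: "Pre-specified landmark analyses will report the proportions achieving continence by age 5 and age 10 for each disease", with the stated purpose "to allow benchmarking against published ARM and HD cohort data".
- **Loss to follow-up.** In survival analyses "the loss will be treated as censoring at the date of last confirmed contact". This covers children who do not come back, not those who miss a form and return.

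**The concern.** A child who becomes continent between two assessments is recorded at the second. If a form is missed, the record slips to the next completed one. The data are interval-censored, and the plan always uses the right-hand end of the interval as the event time. Kaplan–Meier and Cox are built for exact or right-censored times, so the error runs one way: recorded onset is never earlier than true onset.

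This matters most at age 5, because only two or three scheduled assessments can have taken place by then. By age 10 there have been enough that the delay costs little. The age-5 figure is meant to be set beside published cohorts, and the limitations section leans on both landmarks as estimates free of the change of respondent at age 12. A figure that depends on visit timing and form completion is a weak basis for either use.

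**Working it through.** **The plan's own figures.** The protocol states no proportion continent by age 5 or 10. The only related figures are in the sample size section: 0.30 × 480 = 144 and 0.35 × 680 = 238, against a stated 145–240 events; 145/10 = 14.5 and 240/10 = 24, against a stated 14–24 covariates. These reproduce, but say nothing about the size of the delay.

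**Inputs from the protocol.** Annual assessment from age 3; completion p = 0.8 or 0.7 per visit; event dated at the first positive visit; landmarks at ages 5 and 10.

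**Assumptions, because the protocol is silent.** Onset is even between 3 and 5, with none before 3. Forms are missed independently, and a missed form costs a full year. The landmark is the exact fifth birthday, with a visit on that day counted.

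**Visits on birthdays.** Half of onsets fall between 3 and 4 and have two chances to be recorded by age 5 (visits at 4 and 5). The other half have one chance (the visit at 5).

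Shortfall = 1 − [0.5(1 − (1 − p)²) + 0.5p]

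- p = 1: 1 − (0.5 + 0.5) = 0%
- p = 0.8: 1 − (0.5 × 0.96 + 0.40) = 12%
- p = 0.7: 1 − (0.5 × 0.91 + 0.35) = 19.5%

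**Visit months spread evenly over the year.** On average a quarter of onsets have two chances, half have one and a quarter have none before the fifth birthday.

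Shortfall = 1 − [0.25(1 − (1 − p)²) + 0.5p]

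- p = 1: 1 − (0.25 + 0.50) = 25%
- p = 0.8: 1 − (0.25 × 0.96 + 0.40) = 36%
- p = 0.7: 1 − (0.25 × 0.91 + 0.35) = 42%

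The mean delay with spread visits is 0.5 + (1 − p)/p years: 0.75 at p = 0.8 and 0.93 at p = 0.7.

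**Varying the assumptions.** Simulation of 400,000 children per setting, with a constant onset hazard from age 3 that gives 30% by age 8. Relative shortfall at age 5:

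| Setting | p = 1 | p = 0.8 | p = 0.7 |
|---|---|---|---|
| Birthday visits, none continent by 3 | 0% | 12% | 19% |
| Birthday visits, 20% continent by 3 | 0% | 5% | 8% |
| Spread visits, none continent by 3 | 24% | 35% | 41% |
| Spread visits, 10% continent by 3 | 13% | 21% | 27% |
| Spread visits, 20% continent by 3 | 8% | 15% | 20% |
| Visits 0–3 months after birthdays, none continent by 3 | 42% | 52% | 58% |

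The last row shows what hangs on the landmark definition: read as the exact birthday, it excludes an age-5 visit held a few weeks late.

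**Age 10**, none continent by 3, over the onset patterns tried: about 3–4% (p = 0.8) and 5–6% (p = 0.7) with birthday visits; about 8–11% and 10–13% with spread visits.

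**Do the planned methods correct it?** Multiple imputation is for covariates. Mixed models and GEE are for scores. Censoring weights reweight children but do not move an event date, and the half-year delay with spread visits exists even at full completion. The delta adjustment shifts imputed scores in the unfavourable direction only. The rule for more than 40% missingness is not reached at the expected 20–30%. None of them treats onset as lying between two assessments in a child who returns.

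**The case against.** - **The size is not in the documents.** A reader might infer a flat understatement of a quarter to two fifths. That needs spread visit months and no continence before age 3, and its lower end needs full completion, which the protocol does not expect. The schedule is expressed by age, and the section on data abstraction refers to age windows, so visits near birthdays are at least as natural a reading. This objection stands: only a conditional range can be given.
- **A missed form need not cost a year.** The continence instruments are prioritised at each visit, sent out beforehand and available on paper, and surveys may be completed between encounters or by telephone. This stands in part: the calculation may overstate the delay from missed forms, but the gap between annual assessments remains.
- **Benchmarking.** A reader might infer that the registry will look worse than its comparators. The documents do not show how the published cohorts dated continence. If they too relied on visits, they may share the delay.
- **Hazard ratios.** A reader might infer that the Cox estimates are biased too. That could happen if completion differed by a covariate such as deprivation, but it has not been shown.
- **Non-response is not ignored.** The weights in the survival models are motivated partly by informative non-response, and completeness must be reported with every outcome. That is so, but it does not repair the event date.
- **First documented continence is a coherent endpoint.** True, and visit-dated analysis is common. But the landmark is worded as the proportion achieving continence by an age, which is a different quantity.

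**Conclusion.** The concern holds as a matter of direction, and only conditionally as a matter of size. The protocol itself fixes the visit date as the event time and names estimators that take it as exact, so this is not a detail left to an analysis plan. The proportion continent by age 5 is understated, or at best unbiased.

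At the protocol's own 70–80% completion, with no continence before 3 and even onset from 3 to 5, the relative shortfall is about 12–20% for birthday visits and 36–42% for visits spread over the year. It falls to about 5–8% with birthday visits and 20% of children continent by 3. It vanishes only if visits fall on birthdays (or the age-5 visit counts) and every form is completed. At age 10 it is about 3–13%. The documents support neither a claim of bias in the hazard ratios nor a claim that comparison with published cohorts would be unfair. This is an inexpensive improvement to make before the first formal analysis.

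**What to change.** In Statistical analysis, Objective 3, and in the primary outcome row of Table 2:

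1. Define the age-5 and age-10 landmarks by a stated assessment window around each age.
2. For each child keep two dates: the last completed negative BCS or BFS and the first completed, confirmed positive one. Treat a child who is positive at the first completed assessment as left-censored; this will apply to some older prevalent cases.
3. Estimate the continence curves and the landmark proportions, by disease, with the interval-censored non-parametric (Turnbull) estimator.
4. Keep the visit-dated Cox and Fine-Gray models as planned, so that competing risks are still handled, and add an interval-censored proportional hazards model as a sensitivity analysis.

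The cost is protocol wording and analysis code. The assessment dates and results are already collected, and the protocol says that no formal analysis has yet been done. The downside is somewhat wider intervals around the landmark proportions and less familiar software.

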### Catchment and representativeness

The Montreal Children’s Hospital is one of two paediatric tertiary care centres in Québec and receives colorectal referrals from across the province, including from Nunavik and the Cree territory of James Bay, as well as selected complex referrals from other provinces. The registry therefore captures a substantial proportion, but not the entirety, of the incident paediatric HD and ARM population in Québec. To quantify representativeness rather than assert it, the age, sex, diagnosis and severity distribution of enrolled participants will be compared at each annual analysis against two external benchmarks: (i) expected provincial case counts, derived by applying published Canadian incidence estimates for HD (2.05 per 10,000 live births [1]) and ARM (approximately 1 in 2,162 births [3,4]) to Québec live-birth denominators; and (ii) the published case-mix of the ARM-Net and PCPLC registries [11,13]. Aggregate, non-identifying information on patients who are approached but decline enrollment (age band, diagnosis, and referral region) will also be recorded so that a non-participation comparison can be reported. Any material divergence, for example under-representation of remote communities or of the most severe Krickenbeck categories, will be reported explicitly alongside registry outputs and taken into account when interpreting external validity.

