## Strengths and limitations

The principal strengths of the COCOE Registry are its prospective, longitudinal design with follow-up to age 18; its use of validated, age-stratified, disease-specific instruments administered in both official languages; its embedding within an established multidisciplinary clinical pathway rather than a parallel research process; and the pre-specification of outcomes, analyses, missing data handling, and adherence metrics before any analysis is conducted.

Several limitations follow directly from the design and should temper interpretation of registry outputs. The registry is single-centre. Although COCOE serves a wide provincial and inter-provincial catchment, its case-mix reflects a tertiary referral pathway and is likely to be enriched for complex, syndromic, and reoperative presentations relative to the population of all children born with HD or ARM in Canada. Families living at a distance from Montréal, families without stable housing or telephone contact, and families whose preferred language is neither French nor English are plausibly under-represented at both enrolment and follow-up; the resulting bias would favour better-resourced families with better measured outcomes, which is the direction that most threatens the validity of continence and quality-of-life estimates. Registry outputs should therefore be read as describing a referred paediatric colorectal population rather than as national incidence or outcome estimates, and comparisons with ARM-Net and PCPLC data should be made with case-mix in mind [11,13]. The registry infrastructure, data dictionary, and REDCap instruments have been deliberately designed to be transferable to additional Canadian centres, and multicentre expansion through CanCORPS is the primary planned mitigation.

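### The age-5 and age-10 continence figures meant for benchmarking are specified by disease only, so a difference in severity mix, in either direction, may be mixed with a difference in outcome

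*Protocol article*

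**What the plan says.** The protocol article, Statistical analysis, Objective 3, states that "landmark analyses will report the proportions achieving continence by age 5 and age 10 for each disease, to allow benchmarking". The comparators named there are published cohorts of each condition. The level of reporting is the disease and the stated purpose is external comparison. In the same paragraph, Krickenbeck category (ARM) and length of aganglionosis (HD) are candidate predictors in the disease-specific Cox models for time to continence. Those models run only once 10 events per variable are reached in the cohort concerned.

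Case-mix is dealt with in two other places. Under Catchment and representativeness, the "severity distribution of enrolled participants will be compared at each annual analysis against two external benchmarks", one of which is "the published case-mix of the ARM-Net and PCPLC registries". Material divergence "will be reported explicitly alongside registry outputs and taken into account when interpreting external validity". Under Strengths and limitations, the centre's case-mix "is likely to be enriched for complex, syndromic, and reoperative presentations relative to the population of all children born with HD or ARM in Canada", and "comparisons with ARM-Net and PCPLC data should be made with case-mix in mind".

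**The concern.** A crude disease-level proportion is a weighted average of the proportions in each severity group, and the weights are the centre's own severity mix. If the benchmark cohort has a different mix, the two crude figures differ even when children of the same severity do equally well in both.

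The planned safeguards tell the reader that the mixes differ, but they do not change the estimate. Nor do they supply what a reader would need to change it, which is continence by severity group at ages 5 and 10. The data sharing statement does not fill this gap. It provides the aggregate data behind published tables and figures, so what is not tabulated is not released, and individual-level data require a committee decision.

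The Cox models do adjust for severity, but they give hazard ratios within the registry, not proportions by age that can be set beside a published cohort. If the events-per-variable threshold is not met, the plan limits that cohort to descriptive and unadjusted comparisons, and the crude landmark figure could become the main external comparison. The limitations section accepts that adjusted analyses may be delayed in HD, the smaller cohort.

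**Working it through.** **The plan's own figures.** The documents give no landmark proportion, no continence rate by severity and no severity mix, so there is no stated figure to reproduce on this point. The nearby feasibility projection reproduces and is not in question: 480 × 0.30 = 144 and 680 × 0.35 = 238 events, against a stated 145–240.

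**Formula.** Take two severity groups with the same group-specific continence in registry and benchmark: p_m (milder) and p_s (severe). Let w be the severe share. Then

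- crude proportion = (1 − w) × p_m + w × p_s
- registry minus benchmark = (p_s − p_m) × (w_registry − w_benchmark)

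Any difference from this formula is case-mix alone, because the group-specific results are equal by construction.

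**Inputs, all assumed.** p_m = 40–50%; p_s = 10–15%; severe share 30–45% in the registry and 20% in the benchmark.

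- Smallest shift: (0.40 − 0.15) × (0.30 − 0.20) = 0.25 × 0.10 = 2.5 points lower
- Largest shift: (0.50 − 0.10) × (0.45 − 0.20) = 0.40 × 0.25 = 10.0 points lower
- Equal shares: 0

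**One case in full.** With p_m = 45%, p_s = 10%, and severe shares of 35% (registry) and 20% (benchmark):

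- registry crude = 0.65 × 0.45 + 0.35 × 0.10 = 32.75%
- benchmark crude = 0.80 × 0.45 + 0.20 × 0.10 = 38.00%
- difference = −5.25 points
- registry standardised to the benchmark mix = 0.80 × 0.45 + 0.20 × 0.10 = 38.00%, difference 0

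Swapping the two severe shares gives +5.25 points, so the registry would then look better than the benchmark for the same reason.

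**Sensitivity to the assumptions.** Set the benchmark severe share at 35% and the registry share at 45–60%. Continence of 30% and 20% (milder, severe) gives a smallest shift of 0.10 × 0.10 = 1.0 point. Continence of 50% and 5% gives a largest shift of 0.45 × 0.25 = 11.25 points.

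**Scale.** The published ARM range in the sample size section, 24–30%, is 6 points wide, though the protocol does not say that it refers to age 5 or age 10. The simple binomial 95% half-width at 30% is 1.96 × √(0.30 × 0.70 / n): 5.2 points at n = 300, 9.0 at n = 100 and 12.7 at n = 50. A case-mix shift in the assumed range can therefore be as large as the sampling error at n = 300, and the last two values show how intervals widen in small severity groups.

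**The case against.** The strongest reply is that the plan does not ignore case-mix. It measures the severity distribution against external benchmarks every year, commits to reporting material divergence beside the outputs, and says that its outputs describe a referred population. No test, decision rule or judgement of centre performance hangs on the landmark figures. They have a second purpose too: both fall wholly within the proxy-report period. Finer tabulation of a descriptive proportion is often left to a statistical analysis plan, which is not shown here, and reporting by disease does not forbid a further split.

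Much of this stands, and it keeps the point modest. What remains is that the article itself fixes the analysis, its level and its benchmarking purpose, and the safeguard it names is narrative and not carried into the estimate.

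A reader might infer that the plan expects a more severe case-mix than its comparators, so that the centre will look worse than it is. The documents do not support this. The expected enrichment is relative to all children born with HD or ARM in Canada, not to ARM-Net, PCPLC or any other published cohort; that difference is left to be measured. The direction is open: the catchment section gives under-representation of the most severe Krickenbeck categories as an example of divergence, and the limitations section names a selection bias towards better measured outcomes.

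A reader might also infer that standardisation is available throughout at no data cost. It is not shown to be. The case-mix to be collected is that of ARM-Net and PCPLC. The 24% ARM continence figure in the Introduction comes from a PCPLC analysis of over 500 patients, whose mix need not equal that of the whole registry. The 39% HD figure is attributed to separate HD cohort data, and no severity mix is indicated for it.

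**Conclusion.** The point holds in limited form. The landmark proportions are specified by disease only, for external comparison, while severity is collected and treated as a candidate predictor of the same outcome. A difference in severity mix may therefore be confounded with a difference in outcome, in either direction. The 2.5 to 10.0 point range rests wholly on assumed group-specific rates and severe shares, and on equal results within groups; it shows that the effect can matter, not that it will occur. Its actual size and sign cannot be determined from the documents. This is a cheap improvement to a descriptive analysis, not an error in the primary analysis.

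**What to change.** In Statistical analysis, Objective 3:

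- Report the age-5 and age-10 proportions also by pre-specified severity group within each disease (Krickenbeck category for ARM, length of aganglionosis for HD), with the rule for collapsing small cells fixed before results are seen.
- Where the benchmark cohort publishes its own severity mix, add a version directly standardised to that mix, and use it for the benchmark comparison. Where it does not, give the severity-specific figures and say that standardisation was not possible.
- Label the disease-level figure as unadjusted for case-mix.

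The severity-specific figures need only data already collected; standardisation also needs the benchmark's published mix. The cost is one extra analysis and wider intervals in small severity groups.
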